### 2.12. Quality Control

Shenzhen Nanshan District People's Hospital will monitor the following aspects of the trial regularly and strictly: the division and training for the research staff, file management, informed consent, protocol compliance, subject recruitment, filling in the CRF, intervention, quality assured system, statistical analysis, and data management.

### 2.13. Investigation of Adverse Events and Safety

Intervention-related AEs might include edema due to bleeding, bending and breaking of the needle, fainting during acupuncture, and retained needle after treatment. During the course of the study, any AEs including the onset of clinical symptoms, degree of symptom severity, persistence time, treatment, and sequelae will be recorded. AEs will be compared between patients in the experimental group and the control group and will be recorded in the CRF and assessed by the research staff at each visit. Serious AEs will be reported to the ethics committee immediately.

### 2.14. Trial Status

Currently, this trial is at the recruitment phase with some subjects being involved.

## 3. Discussion

The similarities between the temporal three-needle and MS6 are as follows: (1) the two are both locating on the side of the skull and (2) the temporal three-needle and MS6 can treat contralateral central motor dysfunction [11, 20]. The differences between the temporal three-needle and MS6 are as follows: (1) the acupoint projecting brain regions are different: the temporal three-needle projects the sensory region and the motor region including the precentral gyrus and the postcentral gyrus, which may be responsible for sensory function and motor function of the limbs [13], and MS6 projects the precentral gyrus [21], which manages autonomous limb movement [20]; (2) the acupoint-related meridians are different: the temporal three-needle connects the Gallbladder Meridian of Foot-Shaoyang (GB), Bladder Meridian of Foot-Taiyang (BL), Stomach Meridian of Foot-Yangming (ST), and Sanjiao Meridian of Hand-Shaoyang (SJ); MS6 connects the Du meridian (DU), BL, and GB; (3) the acupoint stimulation sensation is different: the temporal three-needle is located at the temporal sutures which have a high degree overlap, and the gaps left by this congenital development process can help the needle sensation of the extracranial scalp penetrate deeper into the skull [10, 11, 13]; however, the MS6 stimulation location includes the parietal bone, frontal bone, and temporal bone, which are not the thinnest part of the skull, so the transmission of the acupuncture sensation may be weaker than that of the temporal three-needle. In summary, because of its different projected cortex, diverse-related meridian system, deeper stimulation sensation, and wider dysfunctional treatment (the temporal three-needle focuses on both motor dysfunction and sensory dysfunction), temporal three-needle therapy is now more widely used for ischemic stroke in China.

Studies have found that abnormal brain structures and functions exist in patients after stroke compared with age- and gender-matched healthy controls [53, 54]. In this trial, we will aim to investigate the neuromodulatory effect of sensorimotor network FC of temporal three-needle therapy for ischemic stroke patients with motor dysfunction. First, we will compare the differences in baseline rs-fMRI metrics between the healthy subjects and the stroke patients to confirm the difference between the healthy subjects and stroke patients. Second, to determine the difference due to the temporal three-needle treatment, we will compare the changes in the rs-fMRI metrics between the experimental group and the control group to demonstrate whether motor function alteration is related to brain functional neuroplastic changes after temporal three-needle treatment. Although a large number of studies on the use of temporal three-needle therapy for the treatment of motor dysfunction, speech disorders, dysphagia, and depression after stroke have indicated clinical behavioral effects [11, 14–18], to the best of our knowledge, our study will be the first randomized neuroimaging trial with both a positive control group and a healthy control group to examine the actual effects by means of rs-fMRI.

This study has several strengths. First, the implementation of rigorous randomized, patient-assessor blind, controlled, neuroimaging trial will provide visual and objective evidence about how temporal three-needle treatment improves motor dysfunction in ischemic stroke patients. Second, the combined assessments of rs-fMRI and behavioral data will be used to identify the neuromodulatory effects of temporal three-needle therapy in stroke patients. Third, research based on the FC within the sensorimotor network, and between the sensorimotor network and nonmotor network, is better for understanding the mechanism of temporal three-needle therapy in stroke according to the “scalp-cortex corresponding theory.”

Some limitations of this study should be noted. First, the major limitation of this protocol is its lack of long-term follow-up assessments. Second, there is no sham acupuncture or blank control comparison group for observation. Third, this trial will be conducted in a single center. Fourth, only the patients of left cerebral ischemia with right limb hemiplegia will be recruited in this protocol, and the patients of right cerebral ischemia with left limb hemiplegia will not be temporarily considered enrolled in this trial. We plan to resolve the aforementioned limitations in the future.

In conclusion, the results of this study are expected to explore the neuromodulatory effects and characterize the central mechanism of temporal three-needle treatment on motor dysfunction in hemiplegic stroke patients from the network-level viewpoint of sensorimotor network functional plasticity and to promote widespread application in real-world practice.

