### 2.2. Sample Size Calculation

Our primary outcome will be resting-state FC measured by rs-fMRI. Because millions of voxels are used to indirectly estimate the blood oxygen level-dependent (BOLD) signal and traditional power calculations are of no significance [32], we calculated the sample size according to the relevant published articles. Previous rs-fMRI study of the acupuncture mechanisms in stroke had a sample size of 20 cases for the healthy control group [33]. Moreover, a study on the effects of sample size on cerebral response to acupuncture with fMRI had shown that the imaging results in 17 healthy controls were similar to the results of studies with 21 cases [34], which may suggest that approximately 20 subjects maybe a relatively common choice in rs-fMRI studies after acupuncture. The sample size in acupuncture mechanism study using rs-fMRI with stroke patients typically ranges from a few cases to approximately 20 cases [33, 35–37]. Because this trial is a neuroimaging study, the primary outcome will be based on the subjects' MRI image processing, and patients with left cerebral ischemia accompanied by right limb hemiplegia will be enrolled in this study so as to ensure the relative consistency of cerebral ischemia lesions and reveal the neuroimaging mechanism more regularly.

Under the condition of left brain ischemia stroke with right limb hemiplegia in this study, we plan to enroll 20 patients diagnosed with ischemia stroke in each patient group (20 in the experimental group and 20 in the control group) and 20 healthy volunteers in the healthy control group.

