### 2.8. Outcome Assessment

The outcome measurements include functional connectivity (FC), regional homogeneity (ReHo), amplitude of low-frequency fluctuations (ALFF), the Fugl–Meyer assessment of upper limb (FMA-UL), the modified Barthel Index (MBI), and adverse events. FC, ReHo, and ALFF will be measured by rs-fMRI. The FMA-UL, MBI, and adverse events (AEs) will be assessed by three experienced rehabilitative assessors.

Additionally, the study duration will be 2 weeks. Outcomes will be assessed at baseline and after 2 weeks of intervention. Each subject will have the same assessor for their pre- and posttreatment evaluations.

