#### 2.8.1. Primary Outcome

The primary outcome is resting-state FC. Functional brain alterations in this study will be more sensitive than structural MRI and behavioral performances in detecting the neuromodulatory effect of temporal three-needle therapy.

Resting-state FC analyses can assess synchronous activity between brain regions and be used to study the brain in healthy and disease groups on the brain-network level, which will help to understand (a) markers for diseases, (b) paths to investigate disease mechanisms, and (c) predictors of clinical course [40]. Resting-state FC could serve as a biomarker of motor function recovery in stroke patients with hemiplegia [41]. Stronger FC after stroke correlates with better behavioral outcome [42]. Resting-state FC analysis may offer an invaluable approach to explore functional network reorganization in the brain after stroke. In this study, brain FC plasticity within and beyond the sensorimotor network will be measured by rs-fMRI.

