### 2.9. Brain MRI Protocol

Healthy controls will undergo a baseline brain MRI scan, and patients in the experimental group and the control group will undergo brain MRI scans at baseline and after treatment. All brain MRI scans will be performed with a 3.0 Tesla scanner (SIEMENS Skyra, Germany) in the Department of Radiology, Shenzhen Nanshan District People's Hospital. The parameters of the sequences were as follows.

Structure MRI: prior to brain functional imaging scan, T1-weighted images of three-dimensional whole-brain structure in sagittal position will be collected using MPRAGE sequence with the following parameters: repetition time (TR)/echo time (TE) = 2530/2.01 ms, flip angle (FA) = 7°, field of view (FOV) = 256 × 256 mm^2^, matrix = 256 × 256, 176 contiguous axial slices, slice spacing = 0.0 mm, and slice thickness = 1.0 mm.

T2 FLAIR (fluid-attenuated inversion recovery):T2 FLAIR will be collected using a turbo spin echo (TSE) sequence with the following parameters: TR = 8500 ms, TE = 102 ms, and flip angle = 160°.

Rs-fMRI: resting-state functional images will be performed using an echo planar imaging (EPI) sequence with the following parameters: TR/TE = 2000/30 ms, FA = 90°, number of slices = 36, matrix = 64 × 64, FOV = 224 × 224 mm^2^, and slice thickness = 3.5 mm.

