### 2.11. Statistical Analysis

#### 2.11.1. MRI Data Analysis

The DPABI toolkit [49] will be used to analyze the image data on MATLAB2016 (MathWorks) to detect any functional changes (FC, ReHo, and ALFF) in brain neuroplasticity due to temporal three-needle treatment. After data preprocessing, data-driven approach will be conducted to explore neuroplastic changes in the two patient groups and the healthy control group. Data-driven approaches can automatically obtain the brain functional network from the data [50]. Independent component analysis (ICA) based on data-driven approaches is not required to assume a priori that the MRI signal can be separated directly into a series of maximally independent components and associated time courses [51, 52] and different components corresponding to the corresponding resting-state network. FDR correction will be used for multiple comparisons to control the false positivity rate. Pearson's correlation analysis will be utilized to study the relationship between the rs-fMRI metrics and behavioral data.

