#### 2.11.2. Clinical Behavioral Data Analysis

In this study, statistical analyses will be performed by intent-to-treat (ITT) analysis and per-protocol (PP) analysis. The ITT analysis will include not only all patients with valid results but also randomized patients who were discontinued for a period of time for some reason or transferred to another group. For missing values, we will carry over the last observation results to the endpoint so that the number of patients at the endpoint of each group will be the same as that at the beginning of the trial. The PP analysis will be applied to subjects who adhere to the protocol, have good compliance, and complete the process. When differences in the results exist between the two analyses, the final clinical trial results will be discussed and explained. In this study, only those who received more than 70% of the interventions will be considered satisfied compliance. That is to say, in total number of the 10 treatments, subject missing more than 3 treatments will be excluded from the PP analysis due to violation of the protocol.

All differences in the baseline demographic and clinical characteristics between the two patient groups will be analyzed with the chi-squared test or Fisher's exact test for categorical data and with the *t*-test or Wilcoxon rank-sum test for continuous values. Continuous variables will be shown as the means, SDs. Categorical variables will be described as frequencies or percentages. 

All tests will be two-sided, and a *p* value <0.05 will be considered statistically significant. If the difference of the primary endpoint between the experimental group and the control group was statistically significant, the results of the experimental group are superior to that of the control group, and the intervention method could be considered as effective. Therefore, we firstly set the type I error of the primary endpoint at 0.05. If significant, we then go to test the secondary endpoint at 0.05 type I error.

The changes in the FMA and the MBI between pre- and postacupuncture therapy will be analyzed using repeated measures analysis of variance (ANOVA), This analysis will be used to compare differences and to examine the group effect, time effect, and time-group interaction effect.

A post hoc test will be conducted. Within-group differences between pre- and posttreatment will be compared using the paired *t*-test or Wilcoxon signed rank test for continuous data. 

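### The between-arm comparison of FC, ReHo and ALFF is described only as a comparison of changes, with no baseline adjustment named; using each patient's own baseline scan as a covariate would be more precise at almost no cost

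*Protocol article*

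**What the plan says.** Section 2.8.1 fixes the endpoint: "The primary outcome is resting-state FC". Section 2.8 puts the two secondary imaging metrics on the same footing: "FC, ReHo, and ALFF will be measured by rs-fMRI". Section 2.9 provides the paired data: "patients in the experimental group and the control group will undergo brain MRI scans at baseline and after treatment"; Table 1 shows the same two scans.

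One sentence, in the Discussion, says how the patient arms are contrasted on these metrics: "we will compare the changes in the rs-fMRI metrics between the experimental group and the control group". It names no test, model or covariate. Section 2.11.1 names the DPABI toolkit, independent component analysis, Pearson correlation with the behavioural data, and a multiplicity rule ("FDR correction will be used for multiple comparisons to control the false positivity rate"). It gives no between-arm model.

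Section 2.11.2 attaches the superiority conclusion to this contrast ("If the difference of the primary endpoint between the experimental group and the control group was statistically significant") and tests the secondary endpoints only if it is significant. Section 2.2 sets the size at "20 in the experimental group and 20 in the control group", on precedent from published studies and without an effect size, SD or power.

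**The concern.** A plain change score fixes the slope of the post-treatment scan on the baseline scan at 1. Unless the pre-post correlation is perfect, the best slope is below 1. Subtracting the whole baseline then adds noise and over-corrects chance baseline differences: an arm that starts low by chance tends to show a larger rise through regression to the mean. A model with baseline as covariate estimates the slope from the data and avoids both effects.

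The stake is precision on the test that decides superiority and opens the secondary endpoints. With 20 patients per arm, no documented power margin and an FDR correction on top, efficiency that can be had from data already collected is worth taking.

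**Working it through.** **Inputs from the article.** 20 patients per arm (section 2.2); two-sided 0.05 (section 2.11.2); baseline and post-treatment scans in both arms (section 2.9). The sample size comes from precedent, so there is no power figure to reproduce.

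**Assumptions.** The article gives no pre-post correlation rho, SD or effect size for FC. I take one scalar FC measure, equal pre and post SD (set to 1), and rho from 0.3 to 0.9.

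**Step 1, variance.**
- Change score: 2(1 - rho).
- Post-treatment value adjusted for baseline (ANCOVA): 1 - rho².
- Ratio, change to ANCOVA: 2(1 - rho)/[(1 - rho)(1 + rho)] = 2/(1 + rho), which exceeds 1 for every rho below 1.
- Post-treatment value alone: 1. The change score is worse than this when 2(1 - rho) > 1, that is, when rho < 0.5.

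**Step 2, patients.** ANCOVA matches 20 per arm on change with 20(1 + rho)/2 per arm.

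**Step 3, power.** Noncentral t, 20 per arm. The effect is chosen so that the change score (38 df) has 80% power. ANCOVA (37 df) is then evaluated at that effect, with and without an inflation of 1 + 1/36 for a random covariate.

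| rho | Change variance | ANCOVA variance | Ratio | ANCOVA n per arm equal to 20 on change | ANCOVA power when change has 80% |
|---|---|---|---|---|---|
| 0.3 | 1.40 | 0.91 | 1.54 | 13 | 92.9–93.5% |
| 0.5 | 1.00 | 0.75 | 1.33 | 15 | 89.0–89.8% |
| 0.7 | 0.60 | 0.51 | 1.18 | 17 | 85.0–85.9% |
| 0.9 | 0.20 | 0.19 | 1.05 | 19 | 80.9–81.9% |

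The effects used at rho 0.3, 0.5 and 0.7 are 1.076, 0.909 and 0.704 SD. A simulation with 4000 runs per rho gave variance ratios of 1.49, 1.29, 1.15 and 1.03, slightly below the formula because estimating the slope costs a little at this size.

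**Step 4, chance imbalance.** The baseline difference between arms has standard error sqrt(2/20) = 0.316 SD. The probability that it exceeds 0.3 SD in either direction is about 34%, and 0.5 SD about 11%. Given a baseline difference D, the change estimate is shifted by -(1 - rho)D. For D = 0.5 SD this is -0.25 SD at rho 0.5, -0.15 SD at rho 0.7 and -0.05 SD at rho 0.9. Section 2.5 states no stratification that would limit D.

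**The case against.** A reader might infer that the plan commits to an unadjusted change score. The text does not go that far. The sentence is a general statement of aim in the Discussion. It names no model and excludes no covariate. Change in FC with baseline FC as covariate fits the same words and gives exactly the same treatment effect as ANCOVA on the post-treatment value. Covariates may also sit in an analysis plan that is not shown. This stands, and the point is therefore about what the article states, not about a proven unadjusted analysis.

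A reader might also infer that the planned test is biased or has an inflated type I error. It does not. Under 1:1 randomisation the change comparison is unbiased on average and valid. It is also the same contrast as the time-by-group interaction planned for FMA and MBI, which have two time points. The imbalance in step 4 is a conditional shift and already part of ordinary sampling error: at rho 0.5 a 0.3 SD imbalance moves the estimate by 0.15 SD, about half of the change-score standard error of sqrt(1.00 × 2/20) = 0.316 SD.

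Finally, the power figures rest on an assumed rho, a chosen effect and one scalar measure tested at 0.05. The plan is a data-driven component analysis with FDR correction, so these figures illustrate the gain and do not predict the trial's power. This also stands.

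None of it removes the direction of the result. Under the stated assumptions every rho below 1 favours adjustment apart from the small cost of estimating one slope, and a comparison of changes is the only contrast the article gives for its primary outcome.

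**Conclusion.** The point holds as a precision improvement, not as a validity defect. The article describes the primary between-arm comparison as one of changes and names no baseline adjustment, although the baseline scan exists. If carried out as a plain change comparison, it has about 54%, 33%, 18% and 5% more variance than the adjusted one at rho 0.3, 0.5, 0.7 and 0.9, and it carries a fraction 1 - rho of any baseline imbalance with reversed sign. This assumes equal pre and post variance and a single FC measure; rho is not in the documents. The gain is material at low to moderate rho and slight near 0.9. The claim that missed effects would follow directly is more than the article can support, since it gives neither rho nor an effect size.

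**What to change.** State in section 2.11.1, and align the Discussion sentence, that post-treatment FC (or equivalently its change) is compared between arms in a model with arm as factor and the patient's own baseline FC for the same component, connection or voxel as covariate. The covariate is defined only once the text says which of these the primary FC measure is. Keep the planned FDR correction. Use the same model for ReHo and ALFF. Report the adjusted difference with its 95% confidence interval, and keep raw change as a descriptive summary.

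The cost is one degree of freedom (37 instead of 38 with 40 patients) and passing the baseline value or map into the group model. No new scan, patient or staff is needed. Section 2.14 has the trial still recruiting, and section 2.6 keeps the statisticians blind until the analysis is complete, so the wording can be settled before anyone analysing the data knows the arms.

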## Figures and Tables

**Figure 1 fig1:**
[figure not shown]
Planned flowchart of the trial.

**Figure 2 fig2:**
[figure not shown]
Locations of temporal three-needle therapy in the experimental group (the use of the picture has been allowed by the author [name] and the patient).

**Table 1 tab1:** Study schedule for enrollment, interventions, and assessments.

Study period				
Items	Baseline		Treatment phase	Outcomes assessment
Time points	−1 to −3 days	0 weeks	1–2 weeks	3 weeks
*Enrollment*				
Eligibility screen	×			
Informed consent	×			
Examination		×		
Randomization		×		
*Intervention*				
Healthy control group (*n* = 20)				
Experimental group (*n* = 20)			×	
Control group (*n* = 20)			×	
*MRI scan*				
Healthy control group		×		
Experimental group		×		×
Control group		×		×
*Assessment (only in the experimental group and the control group)*				
FMA		×		×
MBI		×		×
*Safety*				
Adverse events			×	×

**Table 2 tab2:** STRICTA checklist (details of intervention).

	Items	Details
(1) Acupuncture rationale	(1a) Style of acupuncture	Temporal three-needle therapy based on the rationale system of the meridian acupoint theory in Chinese traditional medicine, modern neurological theory, and anatomical rationale [10, 11]
	(1b) Reason for the treatment provided, based on the historical context, literature sources, and/or consensus methods, with references where appropriate	Acupoints to be used in this study were temporal three-needle located at the projection area of the sensory area and the motor area on the temporal ear [11]. Based on many previous studies, temporal three-needle therapy is widely used for stroke treatment in China [11, 14–18]
	(1c) Extent to which treatment was varied	Only the experimental group will receive temporal three-needle therapy

(2) Details of needling	(2a) Number of needle insertions per subject per session	3
	(2b) Names of points used	Temporal three-needle
	(2c) Depth of insertion, based on a specified unit of measurement	0.5 inches deep
	(2d) Response sought	“De Qi” sensation
	(2e) Needle stimulation	Manual operation
	(2f) Needle retention time	30 minutes
	(2g) Needle type	Sterilized stainless-steel needle measuring 0.30 × 25 mm (Huanqiu, Suzhou Acupuncture & Moxibustion Appliance Co., Ltd, Jiangsu Province, China)

(3) Treatment regimen	(3a) Numbers of treatment sessions	10 sessions (2 consecutive weeks)
	(3b) Frequency and duration of treatment sessions	30 minutes per day, 5 days per week

(4) Other components of treatment	(4a) Details of other interventions administered to the acupuncture group	All patients will receive basic drugs treatment and conventional rehabilitative treatments (including PT and OT)
	(4b) Setting and context of treatment, including instructions to practitioners and information and explanations to patients	The study will be conducted in Shenzhen Nanshan district People's Hospital, and all information will be provided to the patients

(5) Practitioner background	(5) Description of participating acupuncturists	Acupuncturists after completing 5 years of Chinese medicine undergraduate course with more than 10 years of clinical experience will perform the temporal three-needle interventions

(6) Control or comparator interventions	(6a) Rationale for the control or comparator in the context of the research question, with sources that justify this choice	MS6 will be selected as the comparator in the control group based on traditional Chinese medicine theory
	(6b) Precise description of the control or comparator; if sham acupuncture or any other types of acupuncture-like control is used, provide details as for items 1 to 3 above	Based on previous studies [19, 22], MS6 will be mainly selected as the comparator for temporal three-needle therapy in motor dysfunction with stroke patients; in addition to the basic drug treatments and conventional rehabilitative treatment, only the control group will receive MS6 therapy; item 2 (details of needling) and item 3 (treatment regimen) are the same as the experimental group

